Secondarily, we will serially evaluate clinical outcomes of interest prior to and after the start of therapy. Change in clinical measurements (in addition to spirometry – sweat chloride, weight/BMI, quality of life) will be monitored. A complementary analysis evaluating the percentage of participants with  $\geq 15$  mmol/L decline in sweat chloride will also be reported. With a previously estimated 9.7 mmol/L standard deviation of the change in sweat chloride for successful modulator trials (Boyle et al., 2014; Vermeulen et al., 2017), an anticipated 6% of responders would be expected by chance alone. Therefore, the treatment response prevalence will be compared to a reference rate of 6%. For longitudinal FEV1 through day 28 and for secondary endpoints (absolute change in sweat chloride, QOL questionnaire, and weight/BMI from baseline through day 28), means at each time point and changes over time will be summarized along with corresponding confidence intervals estimated by mixed effects models to account for within-subject correlation.

Changes in FEV1 following treatment with Trikafta™ will be correlated with secondary clinical outcome measures. A non-linear Spearman's correlation coefficient will be estimated for each measure paired with iPS cell responses *in vitro*, with corresponding fitted curves displayed graphically along with coordinates for participant's paired *in vivo* and *in vitro* responses.

For other outcomes of interest including sweat chloride levels, quality of life, and weight/BMI, we will also apply a mixed effect model to examine the change in these measures over the study duration. Models will include a subject-specific intercept, to account for variability among subjects prior to the start of the treatment, and a categorical variable for time (baseline, day 14, day 28, day 56). A Dunnett's post-hoc comparisons procedure will be used to determine which time points demonstrated a significant change from baseline. Using the same mixed effects models, we will include  $\Delta$  Isc as predictors of *in vivo* improvement. We will also test the interaction between time and  $\Delta$  Isc to determine when *in vitro* response is most associated with change in clinical response. Adverse events and other safety endpoints will be tabulated and reported using counts and percentages or means and standard deviations, as appropriate.

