**Protocol Title: Evaluating Trikafta for the treatment of patients with non-cystic fibrosis bronchiectasis (NCFBE)**

subject research, we will evaluate therapeutic response in individual subjects by an interrupted time series (ITS) method. Briefly, in the absence of an independent control group, ITS analysis is a quasi-experimental design in which each subject acts as their own control and is followed serially in time prior to and after an interruption (in this case, the start of treatment). If the treatment has causal impact, the post-intervention time series will have a different level or slope than the pre-intervention series. Time series models also have the power to test and correct for possible cyclical patterns and outliers. Using segmented regression analysis, we will conduct ITS models for each of the subjects enrolled in the trial. A significant change in slope from the pre-treatment period will indicate a significant treatment effect. ITS models will be constructed for each outcome of interest where historical and pre-treatment data are available. The change in slope will also be correlated with the *in-vitro* response using Spearman's rank-order correlation coefficient.

All analyses will be conducted using the intention to treat principal, where all subjects will be included in analysis regardless of how long they took the study medication. Statistical significance will be assessed at the 0.05 level and analyses conducted using SAS v. 9.4 (SAS Institute; Cary, NC).

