#### **Inclusion Criteria:**

- Provision of signed and dated informed consent form
- Stated willingness to comply with all study procedures and availability for the duration of the study
- Male or Female age ≥18
- Radiologic and other clinical evidence leading to a diagnosis of NCFBE
- 1 CF-causing mutation and/or sweat chloride measurement ≥ 30 mEq/L and ≤ 60 mEq/L
- Able to perform spirometry meeting ATS criteria for acceptability and repeatability, and FEV1 40-90 mEq/L
- Clinically stable in the past 4 weeks with no evidence of bronchiectasis exacerbation (prior to Screening AND Day 1)
- Willingness to use at least one form of acceptable birth control including abstinence or condom with spermicide. This will include birth control for at least one month prior to screening and agreement to use such a method during study participation for an additional four weeks after the last administration of Study Drug

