## **Protocol Title: Evaluating Trikafta for the treatment of patients with non-cystic fibrosis bronchiectasis (NCFBE)**

---

We anticipate that the 'lead-in' study (to gain information regarding numbers of individuals with NCFBE who may be eligible for the drug treatment ('main' trial) will primarily include patients at Emory followed with a diagnosis of bronchiectasis (who do not have clinical criteria sufficient for a diagnosis of cystic fibrosis). Approximately 300 participants will be accrued locally into the 'lead-in' study.

Subjects who exhibit a single CF-causing mutation in CFTR and/or sweat chloride 30-60 mEq/L will be approached about their interest in reviewing the consent form for the 'main' study (i.e., involving iPSC derivation and *in vivo* Trikafta™ treatment for 4 weeks). We will enroll 30 subjects accrued locally or via physician referral.

For the 'main' study, we plan to recruit 30 subjects with NCFBE. We intend to include ~50% female and ~50% male subjects age ≥ 18. Subjects will be referred from clinicians participating in the trial (Emory University, Atlanta), or from outside institutions. We anticipate that the study population will be 50% male, but >80% white, since most individuals who are carriers of a CFTR mutation are Caucasian. However, efforts will be made to enroll study subjects from non-Caucasian populations who are eligible (e.g., by conducting full exome CFTR analysis to identify rare CFTR mutations found more frequently among non-white individuals, and utilizing mildly elevated sweat chloride as an entry criterion (i.e., in addition to genotype)). Findings from the 'lead-in' study will be compiled in anonymous fashion and using patient identification numbers as described in Section 8. Because CFTR genotypes and sweat chloride for the 'lead-in' study will typically be conducted in a non-CLIA research laboratory, this screening data will not be included in the patient medical record. For subjects who enroll in the 'main' study, report of genotype and CLIA approved sweat testing will be performed and results entered in the medical record.

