### **25. Setting**

Potential participants in this study will be recruited from the Emory University NCFBE clinic. Studies and tests (pulmonary function analysis, quality-of-life surveys, cutaneous punch biopsies, blood samples) will be performed in the Emory clinic facility. Clinical laboratory measurements will be collected during outpatient visits and analyzed in a CLIA approved laboratory at Emory. Research-related procedures such as CFTR genotyping ('lead-in' study), sweat chloride analysis ('lead-in' study), iPSC derivation, and CFTR biochemical/functional analysis may occur in the laboratories of [name] (HSRB 2nd floor, Emory University) and/or [name] (University of Texas, Houston). Work with UT Houston will be performed under a standard interinstitutional subcontract and statement of work approved by both Emory and UT Houston, as well as approval of the UT Houston IRB. Sweat chloride testing and genotype will be confirmed by a CLIA approved laboratory for all subjects entering the 'main' study.

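### The per-subject interrupted time series admits sweat chloride, whose few pre-treatment values include the one that qualified sweat-entered subjects; the slope-change estimate is then open to regression to the mean and is barely testable

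*Protocol*

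**What the plan says.** All references are to the protocol; no separate SAP is at hand.

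- **Which outcomes enter the ITS.** Section 7 plans a segmented regression for each subject: "ITS models will be constructed for each outcome of interest where historical and pre-treatment data are available". The same section lists the candidates: "For other outcomes of interest including sweat chloride levels, quality of life, and weight/BMI".
- **How the result is read.** "A significant change in slope from the pre-treatment period will indicate a significant treatment effect". The slope change is then correlated (Spearman) with the in-vitro response.
- **Who enters.** Section 11 requires "1 CF-causing mutation and/or sweat chloride measurement ≥ 30 mEq/L and ≤ 60 mEq/L". Sweat chloride is therefore the qualifying value for some subjects and not for others.
- **Which laboratory.** Section 13 says that lead-in sweat tests "will typically be conducted in a non-CLIA research laboratory". Section 25 adds: "Sweat chloride testing and genotype will be confirmed by a CLIA approved laboratory for all subjects entering the 'main' study".
- **When sweat chloride is measured.** The Section 6 schedule gives Screening (Day -28 to -1), Day 1, Day 14, Day 28 and Day 56. Day 1 precedes dosing and is not described as an entry test. Day 56 is the wash-out visit.

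**The concern.** An ITS takes the pre-treatment segment as the subject's own control. That works only if the early points are ordinary draws from the subject's untreated series. For a sweat-qualified subject, the screening value, the lead-in value or both were kept because they fell in a window. Day 1 and all later values were not. If most of the source population lies below the middle of the window, the qualifying values are too high on average and the series drifts down before the first dose.

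The drug is meant to lower sweat chloride. A spurious fall before treatment makes the slope change more positive, so a real benefit is understated. The artefact is absent or nearly so in genotype-qualified subjects. The slope change that is correlated with the in-vitro response would then carry a component that depends on how the subject got in.

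**Working it through.** **1. The plan's own figures.** No figure is given for the ITS. The nearest is the 6% of subjects expected to fall by at least 15 mmol/L by chance with an SD of change of 9.7: 1 - Φ(15/9.7) = 0.061, which agrees. The Section 7 power figures for sweat chloride also reproduce (n=16: 97.0%, 70.3%, 96.2%; n=29: >99%, 93.4%, >99%). The 9.7 is taken as given.

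**2. Within-subject SD.** With independent errors, 9.7/√2 = 6.86 mmol/L. This is an assumption. If part of the 9.7 is variation in drug response, the true value is smaller, and so is the bias below.

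**3. Mean excess of a qualifying value over the subject's true level (b), by simulation.** Source mean and between-subject SD are assumed, because the protocol gives neither.

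| Source mean | Between-subject SD | b, one value selected to 30-60 | b, lead-in and screening both selected |
|---|---|---|---|
| 20 | 8 | 6.62 | 4.53 |
| 20 | 12 | 4.40 | 2.73 |
| 25 | 8 | 4.98 | 3.49 |
| 25 | 12 | 3.44 | 2.15 |
| 45 | 8 or 12 | 0 | 0 |

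Above 45 the sign reverses (-1.0 at mean 50, SD 8, one value selected). For genotype-qualified subjects, with only the upper limit of 60 applied, the excess is -0.02 to -0.5.

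**4. Effect on the slope change, no drug effect.** The model has an intercept, a slope, a level change and a slope change, so each segment has its own line and the bias is minus the bias in the pre-treatment slope.

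*Screening at Day -14 and Day 1 only.* The pre-treatment slope is (Day 1 - screening)/15 per day, so the bias is 28/15 × b = 1.867b per 28 days.
- Both values selected: 1.867 × 2.15 = +4.0 to 1.867 × 4.53 = +8.5.
- Screening alone selected: 1.867 × 3.44 = +6.4 to 1.867 × 6.62 = +12.4.
- With screening at Day -28 the factor is 28/29 = 0.966, and the whole range is +2.1 to +6.4.

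*Lead-in at Day -60 (assumed), screening at Day -14, Day 1.* The times centre on -24.33 with sum of squares 2020.7. The slope change per 28 days weights lead-in by 28 × 35.67/2020.7 = +0.494 and screening by -28 × 10.33/2020.7 = -0.143.
- Both selected: (0.494 - 0.143) × b = 0.351b = +0.8 to +1.6.
- Lead-in alone selected: 0.494b = +1.7 to +3.3.
- Screening alone selected: -0.143b = -0.5 to -0.9.

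Dropping only the lead-in value while keeping a qualifying screening value therefore makes the bias larger. If the lead-in value alone qualified the subject and is left out, the bias is 0.

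**5. Noise and degrees of freedom.** The per-subject SD of the slope change is 28 × √C × 6.86, where C is the slope-change element of (X'X)⁻¹.

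| Visits used | Points | Residual df | SD per 28 days |
|---|---|---|---|
| -14, 1, 14, 28 | 4 | 0 | 26.5 |
| -14, 1, 14, 28, 56 | 5 | 1 | 19.2 |
| -60, -14, 1, 14, 28 | 5 | 1 | 19.9 |
| -60, -14, 1, 14, 28, 56 | 6 | 2 | 7.7 |

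With 0 df no test exists. With 1 df the two-sided 5% critical t is 12.7, and with 2 df it is 4.3. The rows with Day 56 put an off-drug value in the treated segment.

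**The case against.** The other side has real points.

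- **Lead-in values are not named.** Section 7 speaks of historical and pre-treatment data. A reader might infer that the ITS will use lead-in results. The text permits this but does not say it, and historical data could mean clinic records. This point stands. The concern does not depend on it, because the scheduled screening value is also a qualifying value for sweat-entered subjects.
- **Not everyone is affected.** A reader might infer that the pre-treatment slope is biased by construction. It is not. Entry is by genotype and/or sweat chloride, Section 26 expects 10-15% of about 300 clinic patients to carry one mutation, and Section 14 allows up to 30% outside referrals, who may have no lead-in value. The bias also vanishes at a source mean of 45. This stands and limits the claim.
- **The laboratory change.** A reader might infer that a non-CLIA result is a biased result. CLIA status is a certification, and the protocol gives no offset between laboratories. A difference could add bias in either direction, but none can be claimed.
- **Small against the noise.** With a lead-in value, 0.8 to 1.6 is 4-8% of an SD of 19.9. A shift common to all subjects would leave Spearman ranks unchanged. Both are right, although the shift here differs by entry route.
- **Supplementary analysis, detail for a SAP.** The ITS drives no primary endpoint, interim decision or sample size. But the protocol itself fixes the rule that admits the outcome and the rule that reads a slope change as a treatment effect, so the choice is not left open.

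**Conclusion.** The concern holds in a limited form. Followed as written, Section 7 admits sweat chloride to a per-subject slope-change analysis whose pre-treatment segment contains, for sweat-qualified subjects, at least one value selected to lie in 30-60. Under the stated assumptions the slope change is biased by about +1 to +2 mmol/L per 28 days with a lead-in value present (both values selected), and by about +4 to +12 with only screening and Day 1. The direction understates benefit.

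The size rests on an assumed source mean of 20-25, between-subject SD of 8-12, within-subject SD of 6.9 and the visit days used. The protocol's description of these patients as normal or only mildly elevated (Section 3) makes a mean below 45 plausible but does not fix it.

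The bias is smaller than the per-subject SD of about 8-27. With 0-2 residual degrees of freedom, the analysis says little about any one subject even without bias. This is a cheap improvement to a supplementary analysis and does not touch the primary conclusions.

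**What to change.** In the ITS paragraph of Section 7, state that sweat chloride is excluded from the ITS models and from the correlation of slope change with in-vitro response. For the in-vivo/in-vitro comparison of sweat chloride, specify the Day 1-to-Day 28 change, both values from the CLIA laboratory, correlated with ΔIsc (Spearman). Keep the mixed model from baseline that Section 7 already plans, and state that baseline is the Day 1 value and not the screening or lead-in value. Day 1 is not an entry test, so it carries no selection of this kind.

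The cost is about two sentences. Much of the replacement is already in Section 7, which plans Spearman correlations with the in-vitro response and mixed models with ΔIsc. What is lost is one supplementary per-subject analysis. For genotype-qualified subjects, a screening value that was not the qualifying value is also given up for the ITS, but their series would still have only 0-2 residual degrees of freedom.

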**Sample size**

We will test the null hypothesis that the true Trikafta™ response rate of NCFBE individuals is  $\leq 1\%$  vs. the alternative hypothesis that the true Trikafta™ response rate is  $\geq 15\%$ . We will initially enroll 16 subjects. If none of these subjects exhibit a clinical response (defined as  $> 5\%$  improvement of % predicted FEV1 from baseline), the study may be considered for termination. Otherwise, we intend to enroll a total sample size of 29 individuals (or 30 subjects, in the unlikely event that an individual discontinues participation; i.e., subjects who do not complete the study will be replaced). In this design, if Trikafta™ is ineffective, the probability of early termination after 16 subjects is 85% and only a 2.8% chance of concluding the drug is effective (type I error). If Trikafta™ is effective, there is a 90.04% chance of reaching this conclusion. If fewer than 2 patients (of 29 patients total) of the overall cohort show a clinical effect, Trikafta™ will be considered ineffective. To demonstrate the ability of iPS cells to predict clinical benefit, 16 (29) patients will provide at least 80% power to detect a significant Spearman correlation of at least  $r = 0.8$  (.53) between the changes in clinical outcomes with changes in short circuit current as measured in iPS cells. Tabular details of this analysis are provided below. Power calculations were performed using PASS v. 14 (Kaysville, UT) with a two-sided Z-test and a significance level of 0.05.

|                            | Cumulative # of responses | Decision                                                                                                             | 95% Confidence Interval (CI) |
|----------------------------|---------------------------|----------------------------------------------------------------------------------------------------------------------|------------------------------|
| Stage 1: Enter 16 subjects | 0                         | Consider Termination of the trial because the agent is ineffective.
Response rate is <math>\leq 1\%</math> | LB of 95% CI is $< 1\%$      |
|                            | At least 1                | Inconclusive result, continue                                                                                        | 95% CI contains 1%           |

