### **7. Statistical Analysis Plan**

Goals of the 'main' study are to determine the clinical response to Trikafta™ and whether *in vitro* responsiveness of iPS cell-derived airway monolayers predict Trikafta™ effectiveness. Primary outcomes comprise the ability of iPSC-derived monolayers to predict respiratory benefit from Trikafta™ after 4 weeks of *in vivo* treatment. Primary analysis will include an estimate of clinical response rate of Trikafta™ at week 4 of treatment and a 95% confidence interval using the exact method proposed by Blaker (Blaker, 2000). A responder is defined as any subject with an improvement, from baseline, in  $FEV_1 > 5\%$  predicted.  $FEV_1$  will also be considered continuously. A two-sided 0.05 alpha level paired t-test comparing the baseline and week 4  $FEV_1$  measurements, along with the test and 95% associated confidence interval, will be evaluated.

In this study, if at least 15% of subjects meet the definition of responder, we will view this as initial evidence of a favorable result. Overall response rate will be accompanied by an exact 95% confidence interval. To determine the role of iPS *in-vitro* response to Trikafta™, we will compare the  $\Delta$  Isc (change in Isc) among Trikafta™ responders and Trikafta™ non-responders using an ANCOVA test. Additionally, we will correlate the  $\Delta$  Isc obtained from *in vitro* experiments with the change in FEV1% predicted (post minus pre) using Spearman's rank-order correlation with an associated 95% confidence interval. We will also test whether the iPS response reaches a CFTR functional threshold of 30% wild-type levels (a magnitude of activity in primary airway epithelial cells viewed as potentially relevant to clinical benefit). In a sensitivity analysis, we will replicate the FEV1 analysis with sweat chloride responses and determine the *in vivo* response rate.

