**Protocol Title: Evaluating Trikafta for the treatment of patients with non-cystic fibrosis bronchiectasis (NCFBE)**

|                                                                                                                                                                                                                                   |                                   |                                                                                      |                                       |
|-----------------------------------------------------------------------------------------------------------------------------------------------------------------------------------------------------------------------------------|-----------------------------------|--------------------------------------------------------------------------------------|---------------------------------------|
|                                                                                                                                                                                                                                   |                                   | trial (proceed to stage 2).                                                          |                                       |
| Stage 2: Enter 14 additional subjects                                                                                                                                                                                      | 1 or less
(stage I + stage II) | Consider that the agent is ineffective. Response rate is $\leq 1\%$                  | LB of 95% CI is less than 1%          |
|                                                                                                                                                                                                                                   | 2 or more
(stage I + stage II) | Drug may be effective
Response rate is greater than 1% and not different from 15% | 95% CI contains 15% and LB is $> 1\%$ |
|                                                                                                                                                                                                                                   | 6 or more
(stage I + stage II) | Drug is effective
Response rate is at least 15%                                   | 95% CI LB $\geq 15\%$                 |

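### The 1% null for the FEV1 response is not derived, so the stated 85% early stop and 2.8% type I error hold only if chance alone makes no more than about 1% of patients responders

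*Protocol*

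**What the plan says.** Section 7 (Statistical Analysis Plan) sets the endpoint: "A responder is defined as any subject with an improvement, from baseline, in" FEV1 of more than 5% predicted, at week 4. It also says that a response rate of at least 15% will be viewed as initial evidence of a favourable result.

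The Sample size subsection sets the test: "We will test the null hypothesis that the true Trikafta™ response rate of NCFBE individuals is" at most 1%, against at least 15%.

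- Stage 1 enrols 16 subjects. "If none of these subjects exhibit a clinical response", termination may be considered.
- "Otherwise, we intend to enroll a total sample size of 29 individuals" (30 to allow for a dropout).
- "If fewer than 2 patients (of 29 patients total) of the overall cohort show a clinical effect, Trikafta™ will be considered ineffective".
- The stated properties are that, for an ineffective drug, "the probability of early termination after 16 subjects is 85% and only a 2.8% chance of concluding the drug is effective (type I error"), and that power is 90.04%.

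The decision table in the same subsection has two positive tiers. Two or more responders means a possible effect, glossed as "Response rate is greater than 1% and not different from 15"%. Six or more means the drug is effective.

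For the secondary sweat chloride responder endpoint (a fall of at least 15 mmol/L), Section 7 starts from an SD of change of 9.7 mmol/L, states that "an anticipated 6% of responders would be expected by chance alone", and tests against 6%.

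**The concern.** The trial is open label, and Section 7 acknowledges that it has no independent control group. Under an inactive drug, the responder rate is therefore the share of patients whose % predicted FEV1 happens to be more than 5 points higher at week 4 than at baseline. That share depends on the SD of the change between visits. The protocol gives no SD for FEV1 change, no source for 1% and no chance-response argument, although it makes exactly that argument for sweat chloride.

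The stop-or-continue decision at 16 subjects, the final conclusion and the sample size all rest on this input. Responder status also defines the groups for the planned comparison of iPSC short-circuit current, so chance responders would blur that result too.

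**Working it through.** **Inputs.** From Section 7: n1 = 16, continue if at least 1 responder; n = 29, at least 2 responders; null 1%, alternative 15%; FEV1 threshold 5 points; sweat chloride cut-off 15 mmol/L and SD 9.7. Assumed: the SD of the 4-week change in % predicted FEV1 (not in the document), a mean change of zero, and a normal distribution.

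**Step 1: reproduce the stated figures.** X1 ~ Bin(16, p) and X2 ~ Bin(13, p).

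- Early stop at p = 0.01: 0.99^16 = 0.851 (stated 85%).
- Type I error: P(X1=1)·P(X2≥1) + P(X1≥2) = 0.1376 × 0.1225 + 0.0109 = 0.0278 (stated 2.8%).
- Power at p = 0.15, same formula: 0.9004 (stated 90.04%).

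All three agree. With 30 subjects the type I error is 2.9%. If the non-binding stop is ignored it is 3.4% at 29.

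**Step 2: reproduce the sweat chloride allowance.** 1 − Φ(15/9.7) = 1 − Φ(1.546) = 6.1%, matching the stated 6%.

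**Step 3: apply the same formula to FEV1.** The chance rate is p = 1 − Φ(5/SD). Setting p = 1% gives SD = 5/2.326 = 2.15 points.

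**Step 4: properties with no drug effect at other SDs.** Worked case, SD 3: p = 1 − Φ(1.667) = 0.0478. P(0 of 16) = 0.9522^16 = 0.457. P(X1=1) = 0.367, P(X2≥1) = 0.471 and P(X1≥2) = 0.176, so P(at least 2 of 29) = 0.367 × 0.471 + 0.176 = 0.349.

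The three right-hand columns require at least 1 responder at stage 1. The cut-off of 5 represents the 15% benchmark, because 0.15 × 29 = 4.35.

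| Assumed SD | Chance rate | P(0 of 16) | ≥2 of 29 | ≥5 of 29 | ≥6 of 29 |
|---|---|---|---|---|---|
| 2.15 | 1.0% | 85% | 2.8% | <0.1% | <0.1% |
| 2.5 | 2.3% | 69% | 12% | <0.1% | <0.1% |
| 3 | 4.8% | 46% | 35% | 1.1% | 0.2% |
| 4 | 10.6% | 17% | 76% | 18% | 8% |
| 5 | 15.9% | 6% | 92% | 49% | 31% |
| (rate set to 6%) | 6.0% | 37% | 46% | 2.7% | 0.7% |

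Ignoring the interim stop changes the ≥5 column only slightly (19% at SD 4, 50% at SD 5).

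**Step 5: crossing points for the rule of at least 2.** The false-positive rate passes 5% at SD 2.27 (chance rate 1.4%) and 50% at SD 3.30 (chance rate 6.5%). At SD 5 the chance rate of 15.9% exceeds the 15% alternative.

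**The case against.** The strongest reply has four parts.

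- **The figures are correct as calculated.** This stands. A reader might infer that 2.8% is a miscalculation, but it is exact for the hypotheses as stated. What is unsupported is the input, and hence the description of these figures as what happens when the drug is ineffective.
- **The size depends on an SD that the protocol does not give.** This also stands. A reader might infer that the rule will usually call an inactive drug effective. That needs an SD above about 3.3 points, which nothing in the document establishes. The protocol's own 6% gives 46%, just short of half, and it is a sweat chloride figure rather than evidence about spirometry.
- **Two responders is not the only bar.** The decision table reserves its firm conclusion for 6 or more, and the 15% benchmark amounts to 5 of 29. At SD 3 these higher bars are rarely met by chance (0.2% and 1.1%), and the problem returns only at larger SDs. But the stated 2.8% and 90.04% are calculated for 2 or more, which the text equates with concluding that the drug is effective, so the stated error rate has to be judged on that rule.
- **Other analyses do not use the 1% null.** A paired t-test of FEV1 with its confidence interval is planned, iPSC prediction is named as a primary outcome, the stop is non-binding, and Section 20 says that the data are preliminary and not for submission or label expansion. This limits the damage, but it does not justify the stated operating characteristics.

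The point does not belong to a separate analysis plan: the null, cut-offs, interim rule and error rates are all fixed in this protocol.

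**Conclusion.** The concern holds as a conditional statement. The 85% and 2.8% describe an ineffective drug only if about 1% or fewer of patients would gain more than 5 points by chance, which under normality and zero mean change means an SD of at most about 2.15 points. The document neither states nor supports that condition, and it departs from its own sweat chloride reasoning. The margin is small: control at 5% is lost at an SD of 2.27. Beyond that, the size depends on the assumed SD, with the false-positive rate for 2 or more responders running from 12% at SD 2.5 to 92% at SD 5. The protocol cannot show where in that range the trial lies. Because the interim and final decisions rest on these figures, they should be corrected before the rule is applied.

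**What to change.** Before the decision rule is applied, set the FEV1 null as Section 7 does for sweat chloride: the probability of a change above 5 points, from a stated SD of off-drug change.

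- **Source of the SD.** Use an external or pre-specified value. It can be checked against the Screening-to-Day 1 change, but only in subjects tested in the same bronchodilator state at both visits, because Section 6 lets Screening spirometry be pre- or post-bronchodilator.
- **Restate the design at n = 29.** For example, a 6% null with the stage 1 rule unchanged needs at least 5 of 29: type I error 2.7%, power 44% at a true 15% and 88% at a true 25%. Give the error rate for each tier of the decision table and for the 15% benchmark.
- **Interpretation.** Read the responder rate alongside the already planned paired mean change and its confidence interval.

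Averaging Day 14 with Day 28 to reduce noise is not part of this fix. It would change the week-4 endpoint, and its gain relies on independent visit errors.

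The cost is revised wording and a less favourable stated power (44% instead of 90.04% at a true 15% in the example). No patients or visits are added.
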